## Methods

### Study setting

#### Study setting

This naturalistic study will be conducted within Berkshire Healthcare NHS Foundation Trust through Talking Therapies, an NHS IAPT provider, that serves a population of 900,000 across 7 Clinical Commissioning Groups (CCGs), all of which are demographically and economically diverse, ranging from rural West Berkshire to urban commuter towns close to London. Talking Therapies aims to provide an easily accessible and clinically effective service for those within the community who suffer from anxiety and depressive disorders. These objectives were met in the last year by providing a stepped care model of mental health services to over 11,000 individuals. Those wishing to access the service can do so through self-referral, GP referral, or referral from allied services. If suitable, clients are offered treatment either at Step 2 or Step 3 based on their need. Step 2 services include low-intensity CBT-based treatments such as guided self-help, iCBT and group treatment, supported by trained psychological wellbeing practitioners (PWP). Step 3 services include high-intensity face-to-face CBT and counselling interventions, delivered by a variety of counsellors, CBT therapists and psychologists.

#### Trial design

A parallel-groups, randomised controlled trial design will be used to examine the effectiveness and cost-effectiveness of internet-delivered interventions for depression and anxiety disorders against a waiting list control group. Based on the primary diagnosis obtained from the Mini International Neuropsychiatric Interview 7.0.2 (M.I.N.I), participants will be randomised into one of two groups: one for depression and another for anxiety.

Randomisation will follow a 2:1 ratio. For ethical reasons, participants in the control group will receive access to the internet intervention after the waiting list period (8 weeks). The study will be conducted following the CONSORT statement [33], the CONSORT extension for web-based interventions (CONSORT-EHEALTH) [34] and the SPIRIT guidelines (Standard Protocol Items: Recommendations for Interventional Trials) [35]. The SPIRIT checklist can be found in Additional file 1. The study protocol, information on the study, informed consent, and trial related documents have been submitted and approved by the NHS England Research Ethics Committee [REC Reference: 17/NW/0311]. The study flowchart is shown in Fig. 1.

**Fig. 1 Fig1:**
[figure not shown]
Participant flow – CONSORT

#### Sample size

Sample size was determined separately for primary presentations of anxiety disorders and depression for the trial. Using the software program G-power [36] and based on a moderate between group effect size of *d* = 0.5 with a power of 80%, an alpha error of 0.05, and a 2:1 randomisation procedure into immediate treatment and a corresponding waiting list control group. This calculation returned a total sample of 144 participants in the depression arm (96 in the treatment group and 48 in the WL group) and the same for anxiety, leading to a total of 288 participants. To ameliorate against attrition, a 25% uplift was added, resulting a total sample size of 360. Therefore, this number translates to a ratio of *n* = 120 in the treatment group and a corresponding *n* = 60 in the control group for depression, and the same ratio for anxiety. The 2:1 randomisation procedure was implemented to reduce the likelihood of having many people waiting for treatment after presenting to the IAPT service.

#### Eligibility criteria

##### Patient eligibility

All adult users of the Berkshire NHS Trust IAPT Talking Therapies Step 2 services will be eligible to participate. Upon screening participants, the inclusion and exclusion criteria illustrated in Table 1 will be applied. Suitability for an internet intervention is assessed by the PWP based on the willingness of the participants to engage on the iCBT intervention, presence of low to moderate levels of anxiety and depression, no suicidal or self-harm risk, and having internet access.

**Table 1 Tab1:** Inclusion and exclusion criteria

Inclusion Criteria	Exclusion Criteria
Minimum age of 18 years	Suicidal intent/ideation: score > 2 on PHQ-9 question 9
A score of ≥9 on PHQ-9 and/or a score of ≥8 on GAD-7	Psychotic illness
Suitable for an internet-delivered intervention (iCBT)	Currently in psychological treatment for depression and/or anxiety
	Alcohol or drug misuse
	Previous diagnosis of an organic mental health disorder

*Note: PHQ-9* Patient Health Questionnaire-9, *GAD-7* Generalised Anxiety Disorder-7, *iCBT* internet-delivered cognitive behaviour therapy

#### Clinician eligibility

All Psychological Wellbeing Practitioners (PWP), who give clinical support to trial participants, will be eligible to participate in the research that will explore the therapeutic alliance online and the use of therapist behaviours and their relationship to outcomes. PWPs will have received training in the use of the iCBT intervention, the content of the programmes, as well as in delivering feedback when inducted into the service. In addition, all Case Managers providing supervision to clinical supporters of trial participants will be invited to take part in the research and complete the fidelity checklist, which assesses the congruence between the PWP’s written reviews of the clients and the module content they are completing.

##### Recruitment

ᅟ

#### Client recruitment

Recruitment will begin in June 2017 and will continue for 9 months until the numbers are reached or exceeded. Given that prevalence of anxiety disorders is higher than depression, it might be the case that the numbers on the anxiety arm will be reached before the depression arm. If necessary, recruitment on the anxiety arm will be stopped, but patients with primary diagnosis of a specific anxiety disorder will be still offered treatment.

Regarding the recruitment process, firstly, individuals will be given an initial assessment by phone with a Psychological Wellbeing Practitioner (PWP) clinician at Berkshire IAPT service. The assessment will determine if an individual meets the eligibility criteria, and an initial indication of depression, anxiety, or comorbid depression and anxiety will be advised by the PWP. The PWP will then describe the trial and invite the client to participate. Those interested will be assigned a further telephone appointment, to complete a structured clinical interview, the Mini-International Neuropsychiatric Interview (M.I.N.I.) [37]. They will also receive an email with information detailing the study and a link to give consent by means of a digital signature. Upon giving consent, participants will complete the primary and secondary outcomes for the study online (described below). During the M.I.N.I. appointment, the PWP will reiterate details of the research and the programme, describing what is involved and the importance of their participation in the trial. Participants will be allocated to the depression or anxiety arm based on the outcome of the M.I.N.I., and then randomized to the treatment or the waiting-list group. They will be informed of the outcome of randomisation during this appointment. Participants will then receive an email confirming whether they are in the immediate treatment group or waiting list group, and how to proceed. All participants will be informed they are free to withdraw if they no longer wish to take part in the trial. In this case, they will be removed from the trial and they will be offered treatment as usual.

#### Risk management

At assessment, clients are assessed for risk in line with routine clinical practice. This includes an assessment of whether patients can maintain their safety whilst on the waiting list. Those who exceed a clinically determined cut-off for “low-risk” in terms of suicide and/or self-harm on the screening questions will not be eligible to participate in the study and will be referred for additional support (i.e. thoughts of suicide/self-harm may be present but with no active plans, a low level of intentions to act on these thoughts with identified protective factors). Integrated risk measures in the SilverCloud programme allow for monitoring by supporters of any changes in risk for patients throughout the programme. For example, if the patient scores above > 2 on the suicide and self-harm item of the PHQ-9, the user will be prompted to complete 3 qualifying questions in relation to plans, intentions, preparations and protective factors against suicide and self-harm. If required, an alert will be sent through to their clinician, which can then be escalated appropriately within the established clinical governance structure. It is important to note that SilverCloud will not be presented to patients as a programme capable of providing crisis support, and this will be further emphasised through informed consent and the user contract. Once patients have finished the supported period of the intervention, their outcomes on the PHQ-9 and GAD-7 will determine whether they will be appropriately discharged or referred on for further treatment within Berkshire NHS Trust IAPT service.

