**Methods:**

The study is a parallel-groups, randomised controlled trial examining the effectiveness and cost-effectiveness of iCBT interventions for depression and anxiety disorders, against a waitlist control group. The iCBT treatments are of 8 weeks duration and will be supported by regular post-session feedback by Psychological Wellbeing Practitioners. Assessments will be conducted at baseline, during, and at the end of the 8-week treatment and at 3, 6, 9, and 12-month follow-up. A diagnostic interview will be employed at baseline and 3-month follow-up. Participants in the waitlist control group will complete measures at baseline and week 8, at which point they will receive access to the treatment. All adult users of the Berkshire NHS Trust IAPT Talking Therapies Step 2 services will be approached to participate and measured against set eligibility criteria. Primary outcome measures will assess anxiety and depressive symptoms using the GAD-7 and PHQ-9, respectively. Secondary outcome measures will allow for the evaluation of long-term outcomes, mediators and moderators of outcome, and cost-effectiveness of treatment. Analysis will be conducted on a per protocol and intention-to-treat basis.

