### Improving access to psychological therapies

The Improving Access to Psychological Therapies (IAPT) programme involves a five-step approach to psychological care for people with depression and anxiety within the National Health Service (NHS) mental health services [22]. Stepped care models match treatment intensity to client needs by providing the least intrusive and most effective intervention for the client upon entering services. This allows for the effective management of resources, thus increasing access [23].

Step 2 of IAPT allows access to evidence-based treatments by delivering low-intensity psychological support to patients presenting with mild to moderate symptoms of depression and anxiety. These interventions are often delivered by Psychological Wellbeing Practitioners (PWPs), who are predominantly graduate psychologists with further training in delivering low-intensity CBT-based interventions [22].

A key aspect of the success of the IAPT model is its ability to report on outcomes. All services have a requirement to collect data on patients, access times, waiting times, dropout, treatment type, clinical outcomes, employment status, and work and social adjustment. Together, these outcomes collectively inform the success of the IAPT service.

As recommended by the National Institute for Health and Care Excellence [10, 11], the IAPT programme additionally offers computerised cognitive behavioural therapy (cCBT) as a low-intensity, Step 2 intervention for individuals presenting with mild to moderate symptoms of depression and/or anxiety. cCBT and internet-delivered cognitive behaviour therapy (iCBT) are delivered by PWPs, whose support is offered by means of electronic or telephone communication. Digital services in IAPT have been implemented at step 2 to help overcome the common barriers to accessing mental health treatment, such as costs and long waiting lists. There is certainly room for significant growth in these much-needed digital applications in IAPT, as digital use for treatment purposes is at less than 2% [24].

There is now a substantial body of research that supports the efficacy of online delivered CBT for depression and anxiety disorders [25–27] and findings have been transferred into clinical practice. This presents an opportunity to examine the effectiveness of iCBT in a natural setting.

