#### Aims

The overarching aim of the present study is to implement and evaluate the long-term effectiveness & cost-effectiveness of internet-delivered interventions for depression and anxiety disorders within IAPT services. The specific research questions include the following:Are the SilverCloud *Space from Depression and Space from Anxiety* internet-delivered interventions in IAPT effective in treating depression and anxiety disorders, and maintaining outcomes at follow-up, compared to waiting-list groups?Are the SilverCloud *Space from Depression and Space from Anxiety* internet-delivered interventions cost-effective in treating depression and anxiety disorders in IAPT?Are mediators/mechanisms of change and maintenance associated with both post-treatment and long-term effectiveness of internet-delivered interventions for depression and anxiety?

We hypothesize that: a) the iCBT interventions will be more effective than the waiting-list group in treating depression and anxiety disorders; b) the iCBT interventions will be cost-effective compared to the waiting-list group in treating depression and anxiety; c) we expect that mediators/ mechanisms of change including, repetitive negative thinking styles, emotion regulation skills, therapeutic alliance, credibility and expectancy in iCBT, CBT skills usage and therapist behaviours will be identified as positively impacting post-treatment outcomes and maintenance of gains in iCBT.

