### Statistical analysis

The effectiveness of the internet-delivered interventions compared to control will be analysed using the intention to treat (ITT) approach. Participation levels will be monitored throughout the study and reasons for withdrawal or non-compliance of study subjects will be recorded to document bias associated with non-random protocol deviations. Any potential imbalances will be reported and considered fully in interpretation of the trial results. Missing data will be evaluated for randomness and imputed using multiple imputation procedures.

Differences in baseline primary and secondary outcome measures between treatment groups and waiting list control groups will be identified using χ^2^ tests for categorical variables and ANOVAs or t-tests for continuous variables. Efficacy of treatments over time will be measured using mixed effects models. To complement the post-hoc comparisons, the magnitude of change within and between the groups on the primary and secondary outcomes measures will be established using Cohen’s *d* statistic. Bonferroni corrected *p*-values will be reported for multiple comparisons. All statistical analyses will be conducted in SPSS, SAS and R. Results will be presented following CONSORT guidelines for reporting parallel group randomised trials.

The established IAPT definitions of recovery will be used in our analysis, where ‘recovery’ is determined by patients moving from ‘caseness’ at the beginning of the intervention (i.e. scoring ≥9 on the PHQ-9 or ≥8 on the GAD-7) to ‘non-caseness’ at the end of treatment (thus scoring below the cut-off). Two further established measures will be considered: *reliable improvement*, where the patient has a significant decrease in their PHQ-9 / GAD-7 score upon completion of their course of treatment; and *reliable recovery*, where the patient meets the criteria for both recovery and reliable improvement. Thus, a patient who moves from caseness to non-caseness, and does so by showing a significant decrease in their symptom scores, is said to have a reliable recovery [44].

Exploratory analyses, including the use of correlation and multiple regression, will be conducted to explore the role that mechanisms of change and maintenance measures play in the benefits obtained from the interventions. Moderation and mediation analyses may include the use of macros for SPSS and/or bootstrapping for exploring the role that mechanisms of change play on the outcomes.

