## Discussion

Internet-delivered interventions have evolved in the past years. Today we have robust technology platforms that can configure and deliver a range of intervention modules to meet the needs of the patient. SilverCloud Health is a global provider of mental health and wellbeing solutions online, and Berkshire NHS trust has been using SilverCloud interventions which were developed alongside clinicians at IAPT, and are NICE approved and suitable for use at Step 2.

Undertaking the principal aim of this trial will allow for a robust test of the effectiveness of iCBT in treating depression and anxiety symptoms, and the maintenance and cost-effectiveness of these treatment effects in the long-term. Positive results of these main outcome measures will allow iCBT to consolidate itself as not only a valid treatment option, but as an essential component to the care management pathway offered throughout all IAPT services. This should support the expansion of SilverCloud programmes as the leader in the delivery of digital interventions at Step 2 of IAPT. However, the relevance of the results will also likely have implications for the implementation and success of digital interventions for depression and anxiety in health and mental health care systems worldwide.

Investigating potential mediators and moderators of change will contribute to our understanding of key processes in achieving improvement using online-treatments for anxiety and depression. Mediators and moderators of iCBT outcomes have been relatively understudied, but exploring the roles of constructs such as rumination, emotion regulation, therapeutic alliance and CBT skills usage will provide insight into clinical change. This will potentially inform the tailoring of interventions to best address the needs of the targeted population, ultimately leading to the development of more effective treatments.

The proposed economic analysis will add to the current empirical literature in regards to evidence of the cost-effectiveness of internet-based mental health interventions (i.e. iCBT) and will be an innovative analysis of the SilverCloud iCBT interventions. In a context of health care provision where resources are already stretched, cost-effective interventions can only support the delivery of effective mental health services.

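### After week 8 the primary outcome scores decide who gets further IAPT treatment, yet the 3- to 12-month scores are read as maintenance of iCBT effects

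*Protocol article*

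**What the plan says.** Four parts of the protocol article bear on this.

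- **Referral.** Under Risk management, after the supported iCBT period "their outcomes on the PHQ-9 and GAD-7 will determine whether they will be appropriately discharged or referred on for further treatment". The referral is within the Berkshire IAPT service. No threshold is given and no treatment step is named. Study setting shows that the service offers other Step 2 treatments as well as Step 3 face-to-face CBT and counselling.
- **Question and interpretation.** The first research question in Aims asks whether the programmes are "effective in treating depression and anxiety disorders, and maintaining outcomes at follow-up, compared to waiting-list groups". Hypothesis (c) expects mechanisms that "will be identified as positively impacting post-treatment outcomes and maintenance of gains in iCBT". The Discussion says the trial will test "the maintenance and cost-effectiveness of these treatment effects in the long-term".
- **Measurement.** The abstract schedules assessments "at the end of the 8-week treatment and at 3, 6, 9, and 12-month follow-up", and Table 2 lists PHQ-9 and GAD-7 at every follow-up.
- **Analysis.** Statistical analysis names intention to treat, multiple imputation and this: "Efficacy of treatments over time will be measured using mixed effects models". It does not mention therapy received after week 8.

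**The concern.** PHQ-9 and GAD-7 are both the primary outcomes and the basis for further treatment. Patients with poor scores at the end of iCBT are therefore the likeliest to have more therapy before the later assessments. Their follow-up scores then reflect iCBT plus whatever came next, while the stated interpretation credits iCBT.

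The direction is predictable. If the added therapy works, it lowers scores in the patients who would otherwise hold the mean up, so the follow-up curve flatters maintenance. Long-term effectiveness is the trial's overarching aim, and the Discussion wants positive results to secure iCBT's place across IAPT services, so the label on this result matters.

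This is distinct from the lack of an untreated control after week 8. Even with such a control, the trajectory within the iCBT group would not be an iCBT-only result.

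**Working it through.** **1. The plan's own figure.** Sample size gives 144 per disorder (96 + 48) for d = 0.5, 80% power, alpha 0.05 and 2:1 allocation. A two-sided two-sample t-test gives power 0.802 at 96/48 and 0.794 at 94/47, so 144 is reproduced. The point does not depend on this figure. It supplies only the planned 120 iCBT participants per disorder after the uplift, and d = 0.5 as a reference scale.

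**2. Sequence of events.** iCBT runs for 8 weeks, the scores then inform discharge or referral, and outcomes are measured at 3, 6, 9 and 12 months. The week-8 comparison comes before referral and is not touched. The waiting list starts treatment at week 8 (Waiting list control group), so no untreated group remains at follow-up to separate the effect of iCBT from that of later care.

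**3. Size.** The documents give no rate of non-recovery, no uptake of further treatment and no effect of it. All three inputs are assumptions:

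- p, share of iCBT participants not recovered at week 8: 0.40 to 0.60
- u, share of those treated further: 0.25 to 1.00
- g, added gain from that treatment, in SD units: 0.3 to 0.8

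Shift in the all-participant mean = p × u × g. Number treated further per disorder = 120 × p × u.

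| Case | p | u | g | Shift (SD) | Treated further, of 120 |
|---|---|---|---|---|---|
| Low | 0.40 | 0.25 | 0.3 | 0.03 | 12 |
| Middle | 0.50 | 0.50 | 0.5 | 0.125 | 30 |
| High | 0.60 | 1.00 | 0.8 | 0.48 | 72 |

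If effects are additive, a flat observed mean from week 8 onward would be compatible with an underlying worsening of these amounts. As a scale only, the middle case is 0.125 / 0.5 = 25% of the planned d.

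**4. Mechanism measures.** By Table 2, ERQ and expectancy/credibility end at post-treatment, and STAR-P, STAR-C and the therapist behaviours checklist are completed during treatment. Only PBRS-A (to 3 months) and FATS (listed at follow-up only) can be affected by later therapy. FATS counts CBT skills in use, so skills learned in a later course of CBT would register on it.

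**5. Data that could identify later therapy.** The CSRI is taken at baseline, post-treatment and 6 months, and its stated use is costing. It cannot show therapy between 6 and 12 months. The background section on IAPT points to a better source: "All services have a requirement to collect data on patients, access times, waiting times, dropout, treatment type, clinical outcomes".

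**The case against.** The strongest reply is that this is a naturalistic trial within a stepped-care service, analysed by intention to treat. Keeping every score regardless of later care estimates the outcome of starting iCBT in that pathway, which is a legitimate quantity. How the model handles later therapy could also be left to an analysis plan that is not shown. Both points stand as far as they go. What they do not settle is the label: the protocol does not call the result iCBT plus later care, but maintenance of the iCBT effects, beside a rule that directs further treatment by outcome. An analysis plan could add a sensitivity analysis, but the protocol's question and interpretation would still need rewording.

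A second reply is that a score-based rule discharges those who have recovered, so it gives no added therapy to the patients whose gains are to be maintained. That is largely right and confines the problem to the all-participant mean. Recovered patients who relapse and are treated again remain a smaller, separate matter.

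A reader might infer several stronger things that the documents do not support:

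- *That non-recovered patients go to Step 3.* Neither recovery nor Step 3 appears in the referral sentence. Non-recovery is a natural reading, given the caseness cut-offs in Statistical analysis, but it is an inference.
- *That the bias could equal the whole effect the trial is sized for.* That needs extreme assumed inputs, and d = 0.5 is a between-group effect whose only comparison against untreated controls, at week 8, is unaffected.
- *That hypothesis (c) as a whole is confounded.* Only two measures are exposed, and the analyses are labelled exploratory.
- *That the QALYs are contaminated.* A cost-per-QALY analysis may properly include downstream care, provided that its costs are counted too.

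**Conclusion.** The point holds as a conflict between a stated referral rule and a stated interpretation. As written, the plan would credit iCBT with any benefit of later, outcome-triggered care in the all-participant follow-up mean. The direction favours apparent maintenance if later therapy helps. The size is unknown: 0.03 to 0.48 SD, middle case 0.125 SD, all on assumed inputs. The high end requires every non-recovered patient to be treated further and to gain 0.8 SD. It would go too far to conclude that a stable 12-month curve could hide a complete loss of iCBT gains, because at the low end of the range the shift is negligible. The change should be made, but the trial's main randomised result does not depend on it.

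**What to change.** Leave clinical referral unchanged and revise wording, recording and analysis.

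1. In Aims and Discussion, describe the 3- to 12-month result as the outcome of iCBT followed by routine stepped care.
2. From the routine IAPT record, flag the type and start date of any psychological treatment after the supported period, to 12 months. The protocol says that services record treatment type; that usable start dates are held is an assumption to confirm with the site.
3. Keep the all-participant mixed model under the new label. Add a supplementary analysis that accounts for scores after further therapy begins. Also report maintenance among participants recovered at week 8, defined as staying below caseness without re-treatment. Read FATS and the 3-month PBRS-A with the same flag.
4. In the economic analysis, make sure that the costs of further therapy are counted to 12 months alongside the QALYs. The protocol plans 12-month costing for the intervention group, but the CSRI stops at 6 months, so the same extract would help fill the gap.

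The cost is a small record extract and some rewording, with no new patients or visits. The reported maintenance rate will probably be lower than under the present reading.
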